### Procedures

Before applying the intervention protocol, volunteers will be familiarized with assessment procedures and the WBS technique. Volunteers will be evaluated in the afternoon to avoid different physiological responses due to circadian changes; they will be instructed not to drink caffeine, alcohol, or any other stimulant the night before as well as on the day of data collection, and not to perform strenuous exercises the day before data collection. All experiments will be carried out in an acclimatized room, with a controlled temperature between 22 °C and 24 °C (71.6 °F to 75.2 °F) and relative air humidity between 40% and 60%.

### Evaluations (testing procedures or measurements)

All enrolled volunteers will be submitted to anamnesis and the Baecke questionnaire will be administered to collect information about habitual physical activity related to occupation, sports, and leisure activities [18].

After the screening period and signing the informed consent (Additional file 2), the volunteers will return to the laboratory on 4 different days to perform the preoperative evaluations (Fig. 2), which are: 1) maximal CPX; 2) the 6MWT; 3) blood collection; 4) bioimpedance measurements; and 5) isokinetic and isometric peripheral muscle strength and endurance assessments. All evaluations will be performed again following the intervention.

**Fig. 2 Fig2:**
[figure not shown]
Consolidated Standards of Reporting Trials (CONSORT) flow diagram of the study. 6MWT 6-min walking test, CPX symptom-limited or maximum cardiopulmonary exercise testing

The CPX will be performed on a treadmill (Super ATL, Porto Alegre, Rio Grande do Sul, Brazil) using the incremental Bruce protocol. Volunteers will be monitored by a 12-lead electrocardiogram (WinCardio System, Microme, Brasilia, Brazil) supervised by a physician, and encouraged to achieve maximal effort. Heart rate, blood pressure, and subjective responses of dyspnea and fatigue by the CR10 scale [19] will also be measured.

The 6MWT will be performed according to guidelines established by the ATS/American College of Chest Physicians [20]. The object of this test is to walk as far as possible for 6 min over a 30-m corridor. Cardiorespiratory and metabolic variables will be collected breath-by-breath through a portable Oxycon Mobile® ergospirometer (Mijnhardt/Jäger, Würzburg, Germany) throughout the 6MWT.

Blood samples will be collected the morning after a 12-h fast from the upper limb antecubital vein by a qualified professional to quantify fasting glucose levels, insulin, the insulin resistance index by the Homeostasis Model Assessment method (HOMA-IR), and the lipid profile (total cholesterol, high-density lipoprotein cholesterol (HDL-C), low-density lipoprotein cholesterol (LDL-C), very low-density lipoprotein cholesterol (VLDL-C), and triglycerides) [2, 21]. It will also be used to measure the serums concentrations of TNF-α, adiponectin, leptin, and myostatin. These samples will be analyzed by enzyme-linked immunosorbent assay (ELISA) in duplicates using high-sensitivity kits (Quantikine® HS, R&D Systems, Minneapolis, USA) according to the manufacturer’s recommendations [22]. The volunteers will be instructed not to exercise for 48 h preceding the examination and to maintain their usual diet.

Body composition will be obtained by bioelectrical impedance analysis, performed by an InBody 720 device and dual energy x-ray technique using digital absorptiometry (DXA) [23–26]. The use of both equipment for body composition will ensure all data is collected since the DXA scanning area can be limited and compromise some measures due to the larger abdominal circumference of recruited obese patients. Volunteers will be instructed to undergo a 4-h fast, to wear light clothes, not to have any metal objects in contact with their body, to urinate prior to the examination, not to drink alcohol, and not to perform strenuous exercises the day before the examination [23].

Evaluations of concentric and isometric extension of the dominant knee will be carried out using an isokinetic dynamometer (Biodex Multi-Joint System 3; Biodex Medical System, Inc., Shirley, NY) at least 48 h after the last functional test.

Isometric and isokinetic assessments will be performed using a previously described protocol [27]. The highest absolute concentric extensor and flexor torque as well as a BMI-normalized value, the flexor/extensor ratio, total work, power, and quadriceps femoris muscle fatigue at an angular speed of 60°/s will be measured [27, 28]. Volunteer positioning and the alignment of the mechanical axis, as well as the gravitational correction, will be performed as previously described [27]. Standardized encouragement will be provided by a single evaluator to stimulate volunteers to produce their maximal effort during all tests.

### Bariatric surgery

Many patients do not respond effectively to conservative therapeutic interventions and require a surgical approach. In recent years, the Roux-en-Y gastric bypass technique (RYGB) has been the most predominant modality of surgery, and is proven to be safe, leading to low mortality [6, 8]. It combines gastric restriction and reconstruction of intestinal transit through a jejunal loop that looks like the letter Y [8]. RYGB can provide greater weight loss in the long term with a reduction in several risk factors for comorbidities [8, 9].

### Postoperative data collection

In the PO period, the 6MWT and body composition measurements will be performed. These evaluations will occur within 1 week after discharge. Afterwards, volunteers will be randomized to the experimental group or the control group. At the end of the interventional trial, all preoperative evaluations will be performed a second time.

### Intervention protocol (WBS or sham protocol)

Following the PO assessments and subsequent randomization, the volunteers will return to the laboratory to perform the intervention protocol with WBS equipment (Miha Bodytec, Augsburg, Germany) [29] as described in other studies [30–32]. The experimental group (WBSG; *n* = 16) will perform the WBS protocol while the control group (ShamG; *n* = 16) will perform the same protocol without WBS stimulus.

The WBS vests and cuff electrodes allow for simultaneous control and innervation of 14–18 muscle groups or 10 regions (upper legs, upper arms, bottom, abdomen, chest, lower back, upper back, including the latissimus dorsi) with a selectable intensity for each one allowing a total electrode area of up to 2800 cm^2^ [32, 33]. The strain and current intensity can be individually selected and modified during the protocol and be progressively increased during each training session. The parameters will be saved on smart cards to ensure reliable and valid application during the WBS protocol [31, 32].

WBS stimulation will be accompanied by low-intensity movements to allow an effective contraction (maximum voluntary contraction requested by the supervisor) during electrical stimulation. The exercises will be carried out without any additional weights with volunteers in the standing position. Specifically, WBS will be performed in conjunction with 10–14 dynamics: squat, trunk flexion, exercises of upper limbs, and isometric abdomen contraction. In the experimental group, these muscle contractions will be performed simultaneously with an electrical stimulation current. Figure 3 illustrates a volunteer performing the protocol with a WBS vest.

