**Methods/design:**

The present study is a randomized, double-blind, placebo-controlled, parallel groups clinical trial approved by the Ethics Committee of our Institution. Thirty-six volunteers (body mass index (BMI) > 35 kg/m^2^) between 18 and 45 years of age will be randomized to the WBS group (WBSG) or control (Sham) group (ShamG) after being submitted to BS. Preoperative assessments will include maximal and submaximal exercise testing, body composition, blood inflammatory markers, and quadriceps strength and endurance. The second day after discharge, body composition will be evaluated and a 6-min walk test (6MWT) will be performed. The WBS or Sham protocol will consist of 30 daily sessions for 6 consecutive weeks. Afterwards, the same assessments that were performed in the preoperative period will be repeated.

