#### Inclusion and exclusion criteria

Inclusion criteria will be as follows: 1) body mass index (BMI) in class I (30–34.9 kg/m^2^), class II (BMI 35–39.9 kg/m^2^), or class III (BMI ≥ 40 kg/m^2^) obesity range for at least 3 years or more [15]. Patients with a BMI in the 30–34.9 kg/m^2^ range and presenting with associated comorbidities are candidates for BS at the discretion of medical staff and the endocrinologist [15]. Therefore, these patients will also be included in the present study); 2) no response to conventional and conservative treatment (pharmacological or not); 3) aged between 18 and 45 years; and 4) candidates for gastric bypass surgery.

Exclusion criteria will be as follows: 1) orthopedic conditions (arthrosis or pain) or neurological impairments that would preclude physical activity; 2) myocardial infarction within the last 6 months before study initiation; 3) implanted pacemaker or any metallic device; 4) unstable angina; 5) chronic heart rhythm disorders; 6) moderate or severe heart valve disease; 7) consistent history of heart disease; 8) uncontrolled hypertension; 9) uncontrolled and/or insulin-dependent diabetes mellitus; 10) β-blocker use; 11) chronic obstructive pulmonary disease (COPD) or other lung disorders; 12) any contraindication to the cardiopulmonary exercise test (CPX); 13) any health issues that compromise functional capacity testing; 14) distal arteriopathies; 15) any inflammatory, kidney, or liver conditions with documented diabetic neuropathy; 16) cognitive impairments or difficulty in comprehending or adhering to the procedures; 17) smoking; 18) use of drugs; 19) gestation; 20) use of psychotropic medications, anxiolytics, antidepressants, or appetite control medications; 21) postmenopausal women; and 22) concurrent participation in a regular exercise program. Patients with PO complications will also be excluded from this study.

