#### Sample size

The sample size calculation was performed using GPower, Version 3.1.3 (Franz Faul Universität Kiel, Germany), based on a previous study by our group performed on BS patients [16] which showed a difference between the distance walked during a 6-min walking test (6MWT) before and after aerobic training of 49.7 ± 15 m. We hypothesize that we will see an improvement in 6MWT distance following WBS to a similar level as our previous study. Therefore, we projected a sample size that would provide 80% power at a significance level of α = 0.05, detecting a variation of 30% as a favorable outcome. These parameters indicate a sample of five volunteers would be required to investigate functional gains after the intervention.

The primary outcome measure for the study will be the 6MWT distance in meters since the distance walked following interventions in patients with chronic conditions is an important tool to assess the efficacy of interventions that theoretically improve functional capacity [16]. Secondary outcomes of this study are to investigate whether the intervention prevents muscle mass loss and whether there is an association between 6MWT distance with lean mass in kilograms [17]. Therefore, since the performance improvement, the prevention of lean mass loss, and the association between these measures represent important outcomes in the present study, the sample size was recalculated. Based on the bivariate normal correlation model, considering a significance level of 5%, a sample power of 95%, and a strong correlation (> 0.70) between lean mass percentage and 6MWT performance as the main outcome, the calculated sample size was 16 volunteers per group. Anticipating a dropout rate of approximately 15%, a total of 36 patients will be included in the present study.

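### The Abstract randomises 36 patients, but the Intervention protocol section starts treatment with 16 per arm, which leaves out the dropout allowance

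*Protocol article*

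**What the plan says.** Three sections of the Protocol article give the size of the trial.

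- **Abstract, Methods/design:** "Thirty-six volunteers (body mass index (BMI) > 35 kg/m^2^) between 18 and 45 years of age will be randomized to the WBS group" or to sham. The sentence places this step after surgery: the volunteers "will be randomized to the WBS group (WBSG) or control (Sham) group (ShamG) after being submitted to BS". The section on recruitment, randomization and blinding sets a 1:1 ratio, so 36 randomised means nominally 18 per arm.
- **Sample size:** from the correlation model, "the calculated sample size was 16 volunteers per group". Then: "Anticipating a dropout rate of approximately 15%, a total of 36 patients will be included in the present study".
- **Intervention protocol:** for the patients who return to the laboratory after the postoperative assessments and randomisation, "The experimental group (WBSG; *n* = 16) will perform the WBS protocol while the control group (ShamG; *n* = 16) will perform the same protocol" without the stimulus. That is 32 patients.

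The order of events matters. Consent and the preoperative tests come first: the Evaluations section says "After the screening period and signing the informed consent (Additional file 2), the volunteers will return to the laboratory on 4 different days" for the tests before surgery. Randomisation follows discharge and the postoperative assessments (Postoperative data collection). The eligibility section adds: "Patients with PO complications will also be excluded from this study".

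**The concern.** The arms described in the Intervention protocol section are those that begin treatment, not those that complete it. Sixteen per arm at that point equals the requirement before dropout is added. If that section is followed, no margin is left for losses over 30 sessions in six weeks. The Discussion itself notes substantial attrition and poor adherence in exercise programmes after bariatric surgery.

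The Sample size section adds a second uncertainty. It says that 36 will be *included*, but not whether they are counted at preoperative consent or at randomisation. Between those two points lie surgery and, on the natural reading, the exclusion for postoperative complications.

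At stake is the number of evaluable patients the plan can expect, and the count that defines the intention-to-treat set promised in the Statistical analysis section.

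**Working it through.** **Inputs.** Required: 16 per group, 32 in total (Sample size). Dropout: about 15% (Sample size). Planned total: 36 (Abstract and Sample size). Allocation: 1:1 (Recruitment, randomization, and blinding). Starting arms: 16 and 16 (Intervention protocol).

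**Step 1: reproduce the plan's 36.**
- Dividing by the retained fraction: 32 / (1 − 0.15) = 37.6, so 38.
- Multiplying by one plus the rate: 32 × 1.15 = 36.8, so 37.

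The stated 36 is one or two patients below these. With a rate given as approximate, that is close enough to show where 36 comes from: it is 32 plus a dropout margin. The loss that 36 covers while keeping 32 is (36 − 32) / 36 = 4/36 = 11.1%.

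**Step 2: compare the sections.** 36 randomised at 1:1 gives 36 / 2 = 18 per arm. The Intervention protocol section gives 16 per arm, 32 in total. The difference of 4 is the whole dropout margin.

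**Step 3: evaluable patients after a 15% loss following randomisation.**

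| Randomised | Evaluable | Per arm |
|---|---|---|
| 32 (Intervention protocol) | 32 × 0.85 = 27.2 | 13.6 |
| 36 (Abstract) | 36 × 0.85 = 30.6 | 15.3 |
| 38 | 38 × 0.85 = 32.3 | 16.2 |

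Only 38 keeps 32 evaluable at the stated rate.

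**Step 4: what the shortfall means for the calculation behind the 16.** This is a correlation model at 5% significance with a correlation of 0.70; whether the test is one- or two-sided is not stated. Exact bivariate-normal power for a correlation in n patients:

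| n | One-sided | Two-sided |
|---|---|---|
| 16 | 94.5% | 89.9% |
| 15 | 93.1% | 87.6% |
| 14 | 91.4% | 84.9% |
| 13 | 89.2% | 81.7% |

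The one-sided figure at 16 is close to the stated 95%. Moving from 16 to 13 costs about 5 points one-sided (94.5 − 89.2 = 5.3) and 8 two-sided (89.9 − 81.7 = 8.2).

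**Step 5: what would follow if 36 were counted before surgery.** The document gives no rate of exclusion before randomisation, so the rates here are assumptions. The last column is 36 × (1 − rate) × 0.85.

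| Assumed rate | Randomised | Evaluable after 15% dropout |
|---|---|---|
| 5% | 34.2 | 29.1 |
| 10% | 32.4 | 27.5 |
| 15% | 30.6 | 26.0 |
| 20% | 28.8 | 24.5 |

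None of this applies if 36 is counted at randomisation, as the Abstract says.

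**The case against.** The strongest reply is that the Abstract settles the matter. It fixes both the number, 36, and the time, after surgery. The Sample size wording, "a total of 36 patients will be included in the present study", is compatible with that. On this view the 16 in the Intervention protocol section is simply the evaluable target carried over, an editorial slip and not an enrolment rule. No section tells a site to stop at 36 consents or at 32 randomised. The flow diagram (Fig. 2), where counts by stage would normally appear, is not shown here.

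Much of this stands. A reader might infer that postoperative exclusions will use up the dropout allowance before anyone is allocated. The document does not support that as a finding. It nowhere equates inclusion with consent, gives no rate of postoperative complications, does not mention cancelled operations, and does not say exactly when the complication exclusion is applied. On the Abstract's reading, losses before randomisation leave the allowance untouched.

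The contradiction in numbers remains. A slip would explain the 16 but does not remove it: as written, it is the size of the arms that start treatment, and it disagrees with 36 randomised at 1:1.

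**Conclusion.** The document contradicts itself on its sample size: 36 randomised in one section, 32 starting treatment after randomisation in another. If the 32 were acted on, a 15% loss would leave about 27 evaluable, 13 to 14 per arm, against the 16 per group it asks for. The point at which the 36 in the Sample size section is counted also needs stating, but any loss before randomisation is an assumption.

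Two limits apply. First, a reader might infer that the primary comparison is underpowered as a result. That does not follow. The 16 per group comes from the correlation between lean mass and 6MWT distance, a secondary analysis; the document's separate calculation for 6MWT distance asks for five volunteers, whatever its merits. The shortfall is therefore against the document's own target and is not a shown loss of primary power. Second, restoring 36 does not by itself secure 16 per arm: at 15% dropout it gives 30.6, about 15 per arm.

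**What to change.** - **Sample size section:** state that 36 is the number randomised, and that patients excluded before randomisation do not count towards it.
- **Intervention protocol section:** change n = 16 to n = 18 per arm.
- **Expected evaluable number:** restate it as about 30 to 31 (about 15 per arm) at 15% dropout, or state the rate that 36 does cover while keeping 32, 4/36 or about 11%. If 32 evaluable at 15% dropout is wanted, randomise 38 (19 per arm).

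The cost is wording in two sections. The number randomised stays at the Abstract's 36, or rises by two if 38 is chosen. Somewhat more than 36 patients may have to consent and complete the preoperative tests.

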**Fig. 3 Fig3:**
[figure not shown]
Whole-body electrical stimulation exercises performed by a recruited volunteer

The sessions will last approximately 20–30 min using a previously described protocol, involving a rectangular wave by a symmetrical bipolar electric pulse [13]. Considering a total of 6 weeks of training for both groups, the WBS protocol will be performed in three nonconsecutive days of endurance alternating with 2 days of training per week. All sessions will occur with the supervision of a trained physical therapist.

The endurance training session will apply a bipolar electrical current with a frequency of 85 Hz and an impulse breadth of 350 μs intermittently with 6 s of electrical stimulation using a direct impulse boost to perform the exercise and 4 s off for rest, with ramp of 0.4 s. The total time under current per session will be approximately 12 min, with approximately 5 min of rest between sets. The strength sessions will consist of the same bipolar electrical current, with a frequency of 30 Hz and impulse breadth of 350 μs intermittently, 4 s of electrical stimulation and 10 s of rest, with ramp of 0.4 s. These sessions will last approximately 8 min, with approximately 5 min of resting between exercises.

The intensity of both sessions is prescribed to reach submaximal levels, which will be adjusted to each region according to disparities of current sensitivity, respecting visual and effective contraction, without volunteer discomfort [30, 31]. To maintain an adequate and tolerable exercise intensity, the BORG scale was used. Thus, volunteers should score between 2 and 3 for the perception of effort in this scale in the endurance protocol and above 5 in the protocol of force [31, 32].

The difference between the WBS and control intervention is that the intensity of electrical stimulation will be switched off in the latter group to avoid any influence of WBS equipment during the exercises. Volunteers will be instructed not to perform any regular exercise activities, being questioned weekly with respect to compliance with these recommendations. After the postintervention assessment, the WBS protocol will be offered to the control group.

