## Methods/design

### Study design

The present study is a randomized, double-blind, placebo-controlled, parallel groups clinical trial conducted at the Cardiopulmonary Physical Therapy Laboratory (LACAP) of the Federal University of São Carlos (UFSCar), São Carlos, SP, Brazil. This study was approved by the UFSCar Ethics Committee (number 966.613) and registered at the Brazilian Registry of Clinical Trials (ReBEC, RBR-99qw5h) on 20 February 2015. Recruited volunteers will all provide written informed consent prior to participation. The study will respect the Consolidated Standards of Reporting Trials (CONSORT) as show in the Fig. 1 with the template of content for the schedule of enrolment, interventions, and assessments. The study will also respect the Standard Protocol Items: Recommendations for Interventional Trials (SPIRIT) as shown in Additional file 1, respectively.

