### Volunteers

#### Recruitment, randomization, and blinding

Volunteers will be recruited from among patients included in a waiting list for BS and followed by a multidisciplinary team (composed of a physician, surgeon, anesthesiologist, cardiologist, physical therapist, nutritionist, and psychologist) for a minimum period of 1 year. During this period, volunteers will be counseled on smoking and alcohol cessation and informed about the surgical procedure and PO care.

Eligible volunteers will be evaluated within 1 month before BS, 2 days after discharge and, afterwards, will be randomized to the experimental or control group with a 1:1 allocation ratio by a computer-based permuted block randomization (www.randomization.com). To achieve a gender balance for both protocols, the randomization will be stratified by gender and two randomization plans for each gender will be proposed with blocks of 4. The randomization sequence will be generated by an independent research assistant and the intervention protocol will be applied by a physical therapist. Since the present study is a double-blind clinical trial, the volunteers, the physical therapist who will perform the assessments, and the researcher who will perform the statistical analysis will be blinded to the allocation of the volunteers.

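### Volunteers are said to be blinded, but the arms differ by a felt, visible muscle-contracting current versus no current, so volunteer blinding very probably fails for an effort-dependent primary outcome

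*Protocol article*

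**What the plan says.** The Study design section of the protocol article states: "The present study is a randomized, double-blind, placebo-controlled, parallel groups clinical trial conducted at the Cardiopulmonary Physical Therapy Laboratory". The abstract uses the same description. The section on recruitment, randomization and blinding says who is covered: "the volunteers, the physical therapist who will perform the assessments, and the researcher who will perform the statistical analysis will be blinded". The same section says separately that "the intervention protocol will be applied by a physical therapist"; that person is not listed as blinded.

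The section Intervention protocol (WBS or sham protocol) describes what each arm receives. The active arm exercises in a stimulation suit, with submaximal current adjusted to each region's sensitivity, "respecting visual and effective contraction, without volunteer discomfort". The control arm "will perform the same protocol without WBS stimulus". Later in that section the contrast between the arms is defined: "the intensity of electrical stimulation will be switched off in the latter group to avoid any influence of WBS equipment during the exercises".

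Before the intervention, all volunteers pass through a preparatory step (Procedures): "volunteers will be familiarized with assessment procedures and the WBS technique".

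**The concern.** One part of the article asserts that volunteers do not know their arm. Another gives the arms very different sensory and motor experiences: muscles made to contract by an external current, or nothing. The article mentions no low-level sensory current in the control arm and no explanation to volunteers that would account for feeling nothing.

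This matters because of the outcome. The 6-minute walk test asks the volunteer to go as far as possible. The exercise test and dynamometry also call for maximal effort. Both arms do the same exercises, so the between-group contrast is meant to isolate the current. If volunteers know whether they receive current, that knowledge is confounded with the effect being estimated. Extra effort in one arm, or discouragement in the other, would appear as a treatment effect. A double-blind label would tell readers that this had been controlled.

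**Working it through.** No stated figure is in dispute, so the main check sets the relevant statements side by side.

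1. **Claim.** Volunteers, assessor and analyst are blinded (recruitment, randomization and blinding).
2. **Active arm.** Intensity is tuned to the volunteer's sensitivity and to a visible contraction, stopping short of discomfort. That procedure relies on the volunteer feeling the current.
3. **Control arm.** Same exercises, current off.
4. **Exposure.** Five sessions a week for 6 weeks is 5 × 6 = 30 sessions, as the abstract states. Three per week are endurance sessions with about 12 min under current: 3 × 6 = 18 sessions, and 18 × 12 = 216 min, before counting the strength sessions.
5. **Outcome.** The primary outcome is walk distance (Sample size), an as-far-as-possible test (Evaluations).

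Items 2 to 4 describe an overt difference, repeated many times, with no masking described. Item 1 is therefore very unlikely to hold for volunteers. Nothing in items 2 to 4 undermines the stated blinding of the assessor or the analyst.

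**Illustration of what is at stake.** Suppose there is no true effect, but expectation shifts the mean between-group difference in walk-distance change by b metres. The Statistical analysis section plans an unpaired t test on the change.

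- Inputs: n = 16 per arm (Sample size; Intervention protocol); two-sided 5% level (two-sidedness assumed); SD of 15 m (Sample size, attached to a before-after difference in an earlier aerobic-training study). SDs of 30 and 50 m and all values of b are assumptions.
- Noncentrality: λ = (b / SD) × √(n/2) = (b / SD) × √8 = (b / SD) × 2.828.
- Degrees of freedom: 2 × 16 − 2 = 30; critical value 2.042.
- Probability of a significant result: P(|T| > 2.042), with T noncentral t on 30 df with noncentrality λ.

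Example: b = 10 m and SD = 15 m give λ = 0.667 × 2.828 = 1.886 and probability 0.446.

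| Assumed gap b | SD 15 m | SD 30 m | SD 50 m |
|---|---|---|---|
| 5 m | 15% | 7% | 6% |
| 10 m | 45% | 15% | 9% |
| 15 m | 78% | 28% | 13% |

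Every cell exceeds 5%, but the size varies greatly with the assumptions.

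**The case against.** The strongest defence is that unblinding depends on what volunteers are told. Controls use the same equipment and do the same exercises. If volunteers do not know that active treatment must be felt, some may not infer their arm. The consent form is a supplementary file that was not available for this review. This stands in part: the documents make unblinding very likely, but they do not prove it.

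Several stronger readings are tempting and should not be drawn.

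- **That volunteers have felt the current before allocation.** Procedures mentions familiarisation with the technique but does not say that current is applied. A demonstration of the suit and movements would fit the sentence. The conclusion does not need this step.
- **That the treating therapist's knowledge is a second contradiction.** The article never claims that this person is blinded.
- **That the placebo-controlled description is false.** An inactive device with identical exercise is a sham control, and the article says openly that the current is off, with a reason. Whether the sham is convincing is a separate question from whether there is one.
- **That assessor blinding is also lost.** Volunteers could disclose what they feel, but nothing in the article shows that they would.
- **That 78% or 45% estimates the false-positive risk.** Those figures use the smallest SD in the table, taken from a before-after comparison, and gaps found nowhere in the documents.

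It can also be said that instructions to volunteers and a guess question are operational details that an article may leave out. That is fair, and their absence is not the finding. The finding is the positive statement that volunteers are blinded.

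**Conclusion.** The point holds in limited form. The article states a property, volunteer blinding, that its own description of the arms makes very improbable, and it describes no means of achieving it. Walk distance, maximal exercise testing and dynamometry are therefore open to expectation bias that assessor and analyst blinding does not remove. Blood markers and body composition are less exposed because they do not depend on effort during a test.

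The size of the bias cannot be derived from the documents. With 16 per arm and no true effect, assumed gaps of 10 to 15 m give a significant result between 9% and 78% of the time across SDs of 50 down to 15 m. This shows only that a modest gap could matter. The conclusion rests on the contrast between the arms, not on any one of these figures.

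**What to change.** - In the abstract and Methods, describe the trial as randomised, sham-controlled, and assessor- and analyst-blinded. Withdraw the statement that volunteers are blinded, or qualify it by saying that it was attempted and may not have held.
- Ask volunteers not to discuss sensations during sessions with the assessor.
- At the final visit, record one allocation guess from each volunteer and from the assessor. Take it before stimulation is offered to controls, since that offer reveals the arm. Report the guesses by arm beside the walk result. They should be descriptive only, because a guess made at the end may partly reflect perceived benefit.
- Name expectation bias as a limitation for the effort-dependent outcomes.

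The cost is wording, one brief instruction and one short question; the double-blind label is lost. Recruitment is under way, so the instruction and the question can cover only volunteers still to be assessed, and the date of the change should be documented. Relabelling does not reduce the bias; it stops the report from claiming that the bias was controlled. If the sponsor believes that volunteers stay blinded, the guess data are the way to support that.
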